## Abstract

**Background:**

Clinically significant levels of fear of cancer recurrence (FCR) affect up to 49 % of cancer survivors and are more prevalent among women. FCR is associated with psychological distress, lower quality of life, and increased use of medical resources. Despite its prevalence, FCR is poorly addressed in clinical care. To address this problem, we first developed, and pilot tested a 6-week, 2 h, Cognitive-existential group intervention therapy that targeted FCR in survivors of breast or gynecological cancer. Following the positive outcome of the pilot, we are now testing this approach in a randomized clinical trial (RCT).

*Goal and hypotheses*: This multicenter, prospective RCT aims to test the efficacy of the intervention. The study hypotheses are that, compared to a control group, cancer survivors participating in the intervention (1) will have less FCR, (2) will show more favorable outcomes on the following measures: cancer-specific distress, quality of life, illness uncertainty, intolerance of uncertainty, perceived risk of cancer recurrence, and coping skills. We further postulate that the between-group differences will persist three and 6 months post-intervention.

**Methods:**

Sixteen groups of seven to nine women are being allocated to the intervention or the control group. The control group receives a 6-week, 2 h, structurally equivalent support group. We are recruiting 144 cancer survivors from four hospital sites in three Canadian cities. The sample size was based on the moderate pre/post-test changes found in our pilot study and adjusted to the drop-out rates. *Measurements*: The primary outcome, FCR, is measured by the Fear of Cancer Recurrence Inventory. Secondary outcomes measured include cancer-specific distress, perceived risk of cancer recurrence, illness uncertainty, intolerance of uncertainty, coping, and quality of life. We use reliable and recognized valid scales. Participants are to complete the questionnaire package at four times: before the first group session (baseline), immediately after the sixth session, and 3 and 6 months post-intervention. *Analysis*: In the descriptive analysis, comparison of group equivalent baseline variables, identification of confounding/intermediate variables and univariate analysis are planned. Each participant’s trajectory is calculated using Generalized Estimating Equation models to determine the time and group effects, after considering the correlation structures of the groups. An intent-to-treat analysis approach may be adopted.

**Discussion:**

Our Fear of Recurrence Therapy (FORT) intervention has direct implications for clinical service development to improve the quality of life for patients with breast (BC) and gynecological cancer (GC). Based on our pilot data, we are confident that the FORT intervention can guide the development of effective psychosocial cancer survivorship interventions to reduce FCR and improve psychological functioning among women with BC or GC.

**Trial registration:**

[name] registered the trial with ISRCTN registry (Registration number: ISRCTN83539618, date assigned 03/09/2014).

## Background

According to the 2015 Canadian Cancer Statistics, approximately 42 % of all women will be affected by cancer in their lifetime [1]. Although most cancer patients complete treatment and survive, survivors continue to struggle with fear of cancer recurrence [FCR]. FCR often describes a fear or a worry that cancer will return or progress in the same organ or into another part of the body [2, 3]. FCR is the most common problem reported by cancer survivors [3, 4], with reports ranging from 49 % in prostate cancer survivors to 74 % in lung cancer survivors [5]. A study involving a large cohort of long-term breast cancer survivors (*n* = 2671) found that fear of recurrence was highly prevalent (82 %) [6]. Despite the overrepresentation of women in this sample and that, gender’s association with FCR is still inconclusive although higher mean scores have been observed in women [7], the high prevalence rate underscores the need to address this concern in clinical practice.

While providing clinical care to such large group of cancer survivors may prove difficult, placing priority on individuals experiencing higher levels of FCR may be more feasible. From the literature, there is still no consensus on what constitutes low, moderate, and high levels of FCR. However, some current practice has been to classify low, moderate, and high based on the mean value of the total FCR scores used ± 1 SD [8]. In instances where a clinical cut-off of FCR has been established within a scale [9], this score tends to represent moderate to high levels. From the reported 2671 cohort reported in Koch et al. study [6], the majority had low levels of FCR with 17 % experiencing moderate to high levels. Compared to percentages found in systematic reviews, this percentage is relatively low. Systematic reviews of quantitative studies report prevalence rates of 49 to 66 % for moderate-to-high levels of FCR in cancer survivors [3, 8].

In a less recent cross-sectional study involving 1721 patients with mixed cancer sites and tumor stages, fear of disease progression or recurrence was found to be the most important single distress with 32.2 % of them rating this concern has strongly to very strongly distressed [5]. Their population was very heterogeneous, yet interesting determinants for psychological distress to prioritize for service delivery include patients with gynecological cancers within 6 months after diagnosis and cancer types with much longer treatment duration tending towards the 5-years survival rate criteria. Other systematic reviews demonstrate that high FCR measured at the end of treatment is a strong predictor of high long-term FCR [3, 8, 10, 11]. Overall, there is a trend for FCR to remain stable over the course of post cancer treatment [8].

Moderate-to-high levels of FCR are consistently associated with psychological distress, anxiety, depression, and stress-response symptoms (with correlations ranging from *r* = .19 to .69), suggesting relationships among these constructs, but not a strong overlap [3]. High levels of FCR are also associated with diminished physical and mental quality of life (QoL) [12–16], including increased uncertainty and worry about the future, difficulties making decisions about the future, and fear of death [13]. Cancer patients with high levels of FCR are more likely to refuse transfer from a specialized cancer center and to be followed-up care by a primary care provider [17]. They are less satisfied with their care [18], express doubt about whether their physicians are thorough enough [18], and are more likely to seek readmission to a cancer center [17]. Need for reassurance is often cited as the reason for increased frequency of hospital visits [19]. As such, cancer survivors with moderate-to-high levels of FCR tend to have maladaptive coping reactions, such as hypervigilance, excessive body checking and excessive need for reassurance seeking [20–23].

Despite clear evidence that cancer patients who exhibit moderate-to-high FCR have higher rates of psychological distress and may incur additional medical costs [24], few psychosocial interventions have been empirically tested to reduce FCR [3, 10, 11, 25]. This gap leaves clinicians ill-equipped to guide their patients with empirically tested interventions on how to reduce and cope with FCR. This gap prompted us to conduct a pilot study using a Cognitive-existential group approach. The results of our pilot study have been published [26, 27]. We are now testing the Cognitive-existential group While this approach is further being testing in a clinical trial named the Fear of Recurrence Therapy [FORT] intervention.

### Previous counseling approaches to fear of cancer recurrence

While there are several ongoing trials of FCR interventions [28–30], to date only one published intervention trial has addressed fear of disease progression, a concept related to FCR, in people with cancer or chronic arthritis [31]. This intervention involved both a cognitive behavioral group and a supportive-expressive group, and it successfully decreased fear of disease progression compared to a control group. However, all cancer participants were inpatients admitted to a rehabilitation clinic, and 20 % of them had recurrence or metastases. Hence, the concept of fear of disease progression addressed in this intervention may be more applicable to in-patients with active or advanced disease than to out-patients and those in remissions or with early-stage disease. Another intervention has been developed to address FCR among head-and-neck-cancer patients [32], but results of this trial have not yet been published.

Four additional studies evaluated group therapies designed to improve general psychological wellbeing outcomes for breast cancer survivors and reported on FCR as a secondary outcome. The first study evaluated the impact of a 6-session Mindfulness-Based Stress Reduction (MBSR) group and found a significant decrease in FCR immediately following the six sessions [33]. However, no follow-up study was conducted to evaluate the long-term effectiveness of the intervention, and the study did not include an attention only control group. The second study reported similar findings from an 8-session MBSR group [34] but, again, the study did not include an attention only control group, and the sample was small. The third study reported significant reductions in FCR immediately following a 12-week Emotion Regulation Group [35]. However, improvements in FCR were not sustained at 6 and 12 months after the intervention. Fourth, a telephone intervention designed to improve communication between breast cancer survivors and their physicians did not decrease FCR (the secondary outcome), although the intervention did improve the primary outcome, self-efficacy [36].

As described above, to date no intervention studies have reported an effective means of reducing FCR when it is the primary outcome for out-patient, disease-free survivors, with long-term impact and when the study includes an attention only control group. These gaps prompted us to develop the FORT intervention, a cognitive-existential (CE) group intervention that specifically targets FCR as its primary outcome and includes a structurally equivalent control group with post-intervention measurement at 6 months.

### Rationale for the cognitive-existential therapy intervention for fear of cancer recurrence

Cognitive-behavioural therapy (CBT) tends to be brief and structured, with a focus on skills in monitoring and modifying (in this case cancer-related and underlying fears) thoughts, emotions, and behaviors (e.g., building coping skills, relaxation training, goal setting, problem-solving) [37–39]. Most important for cancer survivors, CBT for health conditions now recognizes the importance of existential issues such as fear of the future and fear of death [37, 38]. Given the existential aspect associated with FCR, we decided to take a therapeutic approach that not only emphasized education, cognitive reappraisal, enhanced coping but also focused on existentially oriented strategies. Since many patients may not readily let go of their maladaptive coping reactions unless they can be helped to accept the ‘unspoken’ part of their experience (their fear of cancer recurrence), it was assessed that CBT alone would not likely help them.

To address patients’ fear, we chose the Cognitive-Existential (CE) approach elaborated by Kissane et al. [40, 41] to guide the development of FORT intervention, along with Lee-Jones et al.’s conceptual FCR model [42]. Themes in the CE approach relevant to our intervention include death anxiety, FCR, living with uncertainty, and future goals [41]. We also designed a group approach, rather than individual because group interventions are as efficacious in reducing distress among cancer patients as individual therapy [43, 44]. Group interventions offer several other advantages as well over individual therapy. In addition to cost-effectiveness, they allow participants to recognize their shared struggle and existential pain, to connect and learn from one another, and to feel understood and valued as they support one another [26]. In our pilot study of the group intervention, the women expressed appreciation in hearing other women’s strategies for dealing with FCR and shared inputs on how to improve the intervention [26]. The shared experiences facilitated group cohesion, making discussing sensitive topics, such as fear of treatment and death, more comfortable.

### Rationale for offering the intervention to breast and gynecological cancer survivors

The target populations for our RCT are breast and gynecological cancer (BC and GC) survivors. Although these two populations have different prognoses, they both have a high prevalence of moderate-to-high FCR [45, 46]. Furthermore, systematic reviews have found few if any differences in FCR scores by cancer type [3, 10, 25]. While testing interventions with more than one cancer type potentially increase the number of confounding factors to control for, it also increases the external validity of the intervention. Our RCT comprises the same two target populations as our pilot study. In the pilot study, analysis by cancer type revealed no group difference in the efficacy of the FORT intervention. We, therefore, expect that the two types of cancer survivors will respond similarly to the FORT intervention in the RCT. However, group assignments to the intervention are by cancer type.

### Aims of RCT

The aim of this RCT is to test the effectiveness of a cognitive-existential (CE) group intervention, the FORT intervention, in reducing fear of cancer recurrence among breast (BC) or gynecological (GC) cancer survivors.

### Research question and hypotheses

The research questions are as follow:

What is the effectiveness of the FORT intervention (2 h group sessions for 6 weeks), compared with a structurally equivalent control group, in reducing FCR in the short term (immediately after the end of the intervention at T2) and in the long term, at 3 months (T3) and 6 months (T4) after the intervention?

The main hypotheses are as follow:Compared to a structurally equivalent control group, BC and GC survivors participating in the FORT intervention will (a) have less FCR and (b) show greater improvement in the following secondary outcomes: cancer-specific distress, coping skills, illness uncertainty, quality of life, intolerance of uncertainty, and perceived risk of cancer recurrence.Group differences will be maintained over the 6 months following the intervention, at T3 (3 months post-intervention) and T4 (6 months post-intervention).

## Methods/design

We are conducting this RCT with four specialized cancer centers in two Canadian provinces. The study is funded by the Canadian Cancer Society and is registered with the ISRCTN under [name] (Clinical Trial No. ISRCTN83539618, date assigned 03/09/2014). Ethical approval has been obtained from all four participating centers. All possible precautions were taken to safeguard the rights and privacy of the participants.

### Participant selection

Patients are eligible to participate if they:Have a confirmed past diagnosis of breast (BC) or gynecological cancer (GC), in stages 0–3;Are disease-free at the start of the group;Are 18 years or older;Have completed treatment, except for targeted therapy or hormonal therapy;Have a score of 13 or greater on the severity subscale of the Fear of Cancer Recurrence Inventory (range 0–36), suggesting clinical levels of fear of cancer recurrence (FCR) [9];Have a score of at least 24 on the cancer-specific distress measure of the Impact of Events Scale (range 0–75), indicating clinical levels of distress [47, 48].Can read and write English; andCan give informed consent.

If participants develop a recurrence in the course of the study, they remain in the group intervention, but their follow-up data are not used in the study.

Patients are ineligible to participate if they:Had a previous cancer recurrence;Are enrolled in another psychotherapy group at the start of the study or during their six sessions;Have an unresolved mental health disorder based on disclosure by the potential participant that may affect the group’s work as assessed by the group leader at the pre-interview session.

### Participant recruitment

We are recruiting 144 BC or GC survivors from four hospital sites: Princess Margaret Hospital and Mount Sinai Hospital in Toronto, Ontario, the Ottawa Hospital in Ottawa, Ontario, and the Jewish General Hospital in Montreal, Quebec. Both the Toronto and Ottawa sites see approximately 300 BC and 250 GC patients a year. The Toronto sites are providing 4 to 5 iterations of the FORT intervention; the Ottawa site is providing 3; and the Montreal site one. Because of the higher number of BC patients than GC patients served by these centers, 75 % of the groups will comprise BC patients. Each group (the FORT and the structurally equivalent group control) comprises 6 to 8 women, but up to 9 women per group are being recruited to accommodate possible drop-outs.

Each recruiting site has placed recruiting posters in its waiting area, as well as beside key elevators that patients use on follow-up visits. We also work with the sites’ medical staff to inform eligible participants about the study and seek their consent to be contacted by a research assistant (RA). When the RA contacts potential participants, she explains the study and screens them for eligibility. Study pamphlets with tear-off forms in which potential participants can give their contact information are also placed in the waiting areas of BC and GC follow-up clinics. A locked drop box is left at each participating sites waiting areas for potential participants to insert their contact information.

Following confirmation of eligibility, patients are scheduled to meet with one of the group leaders for a pre-interview assessment. The goal is to review group-work expectations and to assess whether group work fits with patients’ expectations. If both parties agree that group work is a good match, study information is reviewed, written consent is obtained, and a copy of the baseline assessment questionnaire is given to the patient, along with a stamped, pre-addressed envelope. Potential participants are advised to mail in their baseline assessment questionnaires before the start of the first group session.

### Randomization of participants

Before randomization, all of the following forms are completed by all eligible and consenting participants: (a) eligibility form, (b) consent form, (c) baseline measures, and (d) baseline interview form. Randomization of all recruiting sites is centralized at one recruiting site and is performed by a biostatistician working at arm’s length from the study. The biostatistician does not know the identity of the therapists and gives the group allocations to the study’s RA. The group allocation is concealed to the participants. The participants do not know which groups comprise the FORT intervention or the structurally equivalent control group. Randomization occurs each time 18 BC survivors or 18 GC survivors are deemed eligible at one of the four sites. This ratio of 18 ensures nine women in each group, with a buffer of at least two probable dropouts per group. We achieved this target in our pilot study. Each group is planned to start within 2 weeks of the initial randomization of women to each study arm.

### The fear of recurrence therapy intervention

The FORT intervention is theoretically guided by the FCRM [26, 27], Leventhal’s Common Sense Model [42, 49], Mishel’s Uncertainty in Illness Theory [50], and cognitive model of worry [51].

#### Perceived risk of recurrence

According to Leventhal’s Common Sense Model, FCR is best viewed as a multidimensional construct in which internal and external cues increase perceived risk of recurrence, which in turn heightens FCR [15, 42, 52]. Examples of internal triggers include aches and pains. External triggers include anniversary dates of cancer diagnosis, attending cancer screening appointments, and hearing of a friend with a recurrence. There is evidence that perceived risk may be the link between triggers and FCR, as suggested by Leventhal’s Common Sense Model [42]. Perceived risk of recurrence tends to lead survivors to focus on sensations that, before their cancer diagnosis, would have been viewed as normal or, at least, benign (e.g., occasional pain) and to now interpret these as evidence of recurrence. To influence levels of perceived risk, in the intervention, participants are taught to identify internal and external triggers and their link with FCR.

#### Coping strategies

Once patients perceive a risk of recurrence, there is increased the likelihood of maladaptive coping and behavior such as anxious preoccupation, excessive body checking, and reassurance seeking, including from health practitioners [32]. Strong empirical evidence supports the reciprocal relationship between coping and FCR. Patients with moderate-to-high FCR become preoccupied and report excessive body checking [53], reassurance seeking [3], and avoidance coping such as pushing away intrusive thoughts of possible recurrence [54, 55]. While such coping strategies provide temporary relief at best, they tend to increase FCR over time by feeding hyper-vigilance and reinforcing maladaptive coping behaviors [19, 32, 42]. Our FORT intervention focuses on identifying maladaptive coping behaviors and their consequences and then replacing these with more favorable coping skills.

#### Uncertainty

According to Uncertainty in Illness Theory [50], uncertainty is generated when components of an illness possess the characteristics of inconsistency, randomness, complexity, unpredictability, and lack of information in situations of importance to the individual [56]. Living with constant uncertainty increases psychological distress and perceived risk, and reduces the quality of life [50, 56]. To reduce uncertainty about living with cancer, participants learn about the signs that indicate actual cancer recurrence vs. benign symptoms.

#### Intolerance of uncertainty and faulty beliefs about the benefits of worrying

Cognitive models of worry suggest that worriers have a lower tolerance for uncertainty than non-worriers [51]. Patients with elevated FCR may consider inadequate anything less than the complete certainty that they are cancer-free, which may explain their increased use of coping strategies, such as seeking medical reassurance or body checking. While uncertainty indicates ambiguity associated with cancer and its treatment, intolerance of uncertainty reflects a difficulty in tolerating and coping with even small amounts of ambiguity or uncertainty in facing cancer. Cognitive models of worry also suggest that worriers tend to believe that worrying is beneficial. By worrying, they think they can prevent negative outcomes. In our FORT intervention, participants are taught to challenge their beliefs in the benefits of worry and to develop new coping skills to tolerate better uncertainty.

#### Content and processes of the intervention

Two leaders facilitate each group (for both the intervention and control groups). Table 1 gives the content of the FORT group sessions. Group leaders cannot add new participants once a six-session group has started. This procedure is necessary to enhance group cohesiveness and consistency [57]. At their pre-study-interview sessions, participants are told that, if they are absent for more than one group session, they will be asked to withdraw from the study, because too much material and group process development will have been missed. However, the participants are told that, if they have to be absent for only one session, one of their group leaders will contact them to review the session’s content and the homework to be done before the next session. When participants miss more than one session, they are withdrawn from the group and then invited to join a group that has not yet started. Traveling expenses of both the FORT intervention and the control groups are reimbursed. Both groups are provided with refreshments 30 min before the start of each weekly session to allow group members to settle in and chitchat. This strategy increases group cohesion and facilitates starting the group on time.

**Table 1 Tab1:** Content of the Fear of Recurrence Therapy (FORT) intervention sessions

Session number	Description
1.	- Self-introduction by each participant, with a focus on their experience with fear of cancer recurrence.
	- Introduce major heading of the Fear of Recurrence Therapy (FORT) from the six sessions.
	- Introduce the automatic thought, behavior, and consequence therapy model and the fear of cancer recurrence model (FCRM).
	- Introduce notions of cognitive restructuring and how to identify FCR triggers.
	- Teach and practice progressive muscle relaxation.
	Homework: Practice progressive muscle relaxation daily. Complete thought journal and challenge maladaptive thinking about the fear of cancer recurrence.
2.	- Prepare questions for nurse specialist, who provides education about general cancer screening guidelines and signs of recurrence in Session 3.
	- Help participants deal with the fact that uncertainty can never be eliminated.
	- Discuss ways of regaining a sense of control using Wheel of Life exercise.
	- Teach calming self-talk. Provide participants with relaxation CD audio and instruct them to use calming self-talk phrases with their relaxation CD when appropriate.
	Homework: Listen to CD every day. Practice calming self-talk. Complete thought journal and challenge maladaptive thinking about the fear of cancer recurrence. Prepare questions for the specialist nurse visit in Session 3.
3.	- Visit from nurse specialist.
	- Increase tolerance for uncertainty by discussing acceptable levels of worry.
	- Challenge faulty beliefs about benefits of worry.
	- Decrease maladaptive coping strategies.
	- Teach and practice guided imagery.
	Homework: Practice guided imagery daily. Continue challenging faulty beliefs about benefits of worry. Complete thought journal, adding a column for behaviors to monitor coping strategies that participants are adopting.
4.	- Provide psycho-education about worry and the need for exposure to worst fears.
	- Promote emotion expression and confront specific fears that underlie fear of cancer recurrence.
	- Write down worst-fear scenario.
	- Teach and practice mindfulness using a body scan through breathing exercise.
	Homework: Read worst-fear scenario every day and then do a self-care activity. Practice mindfulness exercises daily.
5.	- Review exposure to worst fear scenario exercise.
	- Discuss ways of coping with some of the feared outcomes.
	- Promote expression of demoralization feelings.
	- Encourage participants to re-engage with important life goals, people or activities they may have given up.
	- Discuss what meanings the future and planning now have for them.
	- Teach and practice mindfulness using eating meditation (Raisin meditation).
	Homework: Challenge their worst fear scenarios into more likely realistic ones. Write down goals and priorities for the future.
6.	- Review all content covered.
	- Discuss future goals.
	- Set new priorities.
	- Promote saying good-bye to the group and provide closure.

At the first session, participants in the FORT intervention receive a binder describing the intervention’s framework as well as each session’s activities. At the beginning of the first session, group leaders review the key goals of the intervention. *The key goals of the FORT intervention are to:*Distinguish worrisome symptoms from benign ones.Identify FCR triggers and inappropriate coping strategies.Facilitate the learning and use of new coping strategies, such as relaxation techniques and cognitive restructuring.Increase tolerance for uncertainty.Promote emotional expression of specific fears that underlie fear of cancer recurrence.Reexamine life priorities and set realistic goals for the future.

The participants are shown the in-group activities and the short assignments to complete at home. The latter reinforce concepts learned during the group sessions and help participants prepare for the next session’s content. At the end of each session, take-home homework’s for the following week is reviewed and, at the beginning of the next session, participants’ homework’s is reviewed. As part of their study package, participants receive a CD or audio file containing six different relaxation techniques (deep breathing, progressive muscular relaxation, guided imagery, body scanning, deep relaxation, and encouraging sleep). Each of these techniques is discussed or practiced in one of the group sessions.

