#### Sample size

The primary study outcome is FCR, as measured by the FCRI [9]. The sample size was calculated based on the moderate changes in FCR we observed in the pilot study from baseline (T1) to 3 months post intervention [27] and in the only published RCT intervention study that addresses the fear of disease progression [78]. A sample size of at least 112 participants ensures our ability to detect an effect size of 0.40, with a power of 0.95 and an alpha level of .05 between pre- and post-intervention FCR measures. Therefore, we plan to recruit eight groups of seven participants, for a total of 56 participants per arm. We are also enrolling an additional two participants per group per arm, to account for possible dropouts (72 per arm). This strategy will yield 144 participants in total.

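### Two unreconciled consequences for missing more than one session, with intention-to-treat only optional, let randomised low attenders be left out of the comparison

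*Protocol article*

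**What the plan says.** Under Content and processes of the intervention, women are told at the pre-study interview that "if they are absent for more than one group session, they will be asked to withdraw from the study". The same paragraph then describes what is done: "When participants miss more than one session, they are withdrawn from the group and then invited to join a group that has not yet started". Groups are closed: "Group leaders cannot add new participants once a six-session group has started". A re-joiner therefore always enters a different, later group.

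Under Randomization of participants, "Randomization occurs each time 18 BC survivors or 18 GC survivors are deemed eligible at one of the four sites", and "This ratio of 18 ensures nine women in each group, with a buffer of at least two probable dropouts per group". Groups are planned to start within two weeks of that randomisation. The section has no rule for a woman who returns after leaving an earlier group.

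On the analysis set, the Methods part of the abstract says "An intent-to-treat analysis approach may be adopted". The Statistical analysis section specifies GEE models over T1 to T4 and does not return to the question. For one other event after randomisation, a recurrence, Participant selection is explicit: the women stay in the group "they remain in the group intervention, but their follow-up data are not used in the study".

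**The concern.** Leaving the study and leaving a group to join a later one are different events with different consequences for the data. If the first sentence is followed, T2, T3 and T4 may never be collected, and no later analysis plan can recover them. If the second is followed, the woman is still in the trial, but the article does not say under which allocation, baseline or schedule.

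Both rules are triggered by attendance, which the assigned content can influence. Table 1 gives FORT weekly homework and a written worst-fear scenario to be read every day. The control group has no homework and no such exposure. If low attendance is related both to arm and to fear of recurrence, leaving those women out compares two selected subsets, and the contrast can be shifted in either direction. A firm intention-to-treat commitment would contain this, but the article makes it optional.

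**Working it through.** **1. The plan's own figures.** From Sample size: 8 groups x 7 women x 2 arms = 112, and 8 x 9 x 2 = 144. The allowance is 1 - 112/144 = 2/9 = 22.2%, or 16 groups x 2 = 32 women. These reproduce. The allowance covers dropouts of every kind. The article gives no rate for missing more than one session and no split by arm, so 22.2% can serve only as an upper-end assumption.

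**2. The two sentences side by side.**

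| | Advance notice to participants | Procedure described |
|---|---|---|
| Trigger | More than one absence | More than one absence |
| Leaves | The study | The group |
| Next step | None stated | Offer of a later group |
| Arm of later group | Does not arise | Not stated |
| T2 to T4 collected | Not stated; would plausibly stop | Not stated |

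**3. Bias from leaving out low attenders.** Let w be the fraction of an arm left out and d the amount, in SD, by which those women's outcomes are worse than those of the women who stay. The arm mean equals the stayers' mean plus w x d, so the stayers look better than the whole arm by w x d. The bias in the FORT-minus-control contrast therefore has size w(FORT) x d(FORT) - w(control) x d(control), in favour of FORT when positive. With a common d this is [w(FORT) - w(control)] x d.

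All values of w and d below are assumptions:

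| Left out, FORT vs control | d = 0.25 | d = 0.5 | d = 1.0 |
|---|---|---|---|
| 10% vs 5% | 0.013 | 0.025 | 0.050 |
| 15% vs 5% | 0.025 | 0.050 | 0.100 |
| 22.2% vs 10% | 0.031 | 0.061 | 0.122 |

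The range is about 0.01 to 0.12 SD. If w and d are equal in the two arms, the bias is zero. If the control arm loses more, the sign reverses.

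For scale, the plan states that "A sample size of at least 112 participants ensures our ability to detect an effect size of 0.40, with a power of 0.95". Against 0.40, the range is 0.0125/0.40 = 3% to 0.122/0.40 = 31%. That ratio is only a guide, because the same sentence ties 0.40 to a pre-to-post comparison and does not define it as a between-arm difference in SD.

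**4. What re-entry leaves open.** A woman withdrawn at her second absence may already have attended up to 6 - 2 = 4 sessions in her first arm. Her next group normally comes from a later block of 18, where she would be either allocated again or placed without randomisation.

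- If 5% to 22.2% of 144 leave their group, that is about 7 to 32 women.
- If all of them re-entered as new participants, there would be 151 to 176 sets of records for 144 women.
- If all were allocated again 1:1, about 4 to 16 would be expected in the opposite arm.

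These are outer limits of what the text does not exclude, not forecasts. Re-entry could be rarer, since groups are formed by cancer type and Montreal plans a single iteration.

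**The case against.** The strongest reply is that much of this is silence in a condensed article, and that stronger readings go beyond the text. Four parts of that reply need separate answers.

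- A reader might infer that the plan is a completers analysis. No section defines a completers or per-protocol set, and GEE does not by itself require complete cases. Where the authors intend to discard data, after a recurrence, they say so; for low attenders they do not. This part stands: the analysis principle is left open, not decided the wrong way. GEE can, however, use only data that were collected.
- A reader might infer that re-joiners change arm, are randomised again or are counted twice, so that randomisation is broken. The article says none of this. A later group in the same arm, with one analysed record, fits the text equally well. This part stands too, so these remain possibilities to close off.
- Being withdrawn from a group need not end the questionnaires or change the arm analysed. That is correct, and it is why the two sentences need reconciling: only the first plausibly ends follow-up.
- A reader might apply the whole 22.2% allowance to FORT with a 0.5 SD deficit and no deficit in control, giving 0.222 x 0.5 = 0.11 SD. That treats every dropout as a low attender and puts the deficit in one arm only. The documents support neither assumption, and a range that includes zero is the honest statement.

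The reply does not remove the point. The attendance rule, the re-entry offer and the optional status of intention-to-treat are all stated in the article. They are not detail left to another document.

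**Conclusion.** The concern holds in a limited form. The article attaches two conflicting consequences to the same behaviour after randomisation and does not commit to analysing women as randomised. Followed as written, it permits low attenders to be left out of a comparison between arms whose demands differ.

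The bias cannot be estimated from the document. Under the assumed, unequal losses and leavers' deficits above it is about 0.01 to 0.12 SD, and it may be nil. Duplicate records and exposure to both arms are not excluded by the text, but neither are they planned in it. The correction still matters before follow-up is complete, because outcomes not collected from women who stop attending cannot be restored in the analysis.

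**What to change.** - **Reconcile the two sentences** under Content and processes of the intervention so that stopping group attendance is separate from leaving the study. The attendance rule itself is for the investigators.
- **Keep follow-up going.** Collect T2, T3 and T4 on the original schedule from every randomised woman who has not withdrawn consent.
- **Commit to the analysis principle.** Replace the optional wording in the abstract, and state in Statistical analysis that intention-to-treat is primary: each woman analysed once, with her original baseline, in the arm first assigned.
- **State the position of re-joiners.** A woman who joins a later group is not randomised again, gives no second set of outcome records and is not counted again toward the 112 or 144. Record which arm the later group belonged to, because analysis by first allocation does not undo exposure to both contents.
- **Report attendance by arm**, and give any completers analysis as sensitivity only.

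No sample-size figure changes: the target remains 144 women, 72 per arm, one set of records each. The cost is protocol wording, some extra mailing of questionnaires, and possibly a smaller estimated effect, since women with little exposure stay in the comparison.
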